### Study population

The source population comprises individuals who are undergoing, scheduled to undergo, or have previously undergone latent TB infection (LTBI) testing at the participating hospitals. Eligible participants include those who (1) are scheduled for LTBI testing, (2) have already completed LTBI testing, (3) are currently receiving TB preventive treatment, or (4) have completed TPT within the past two years.

The inclusion and exclusion criteria are summarized in Table 1. The study targets adults aged 19 years or older, encompassing all individuals eligible for LTBI testing and treatment as defined in the “Korean Guidelines for Tuberculosis (fifth edition, 2024)” [4] and the “National Tuberculosis Control Manual (2025)”. This also includes employees working in congregate settings who are mandated to undergo LTBI screening under the TB Prevention Act [5]. Individuals with a history of treatment for active TB disease are excluded from participation.

**Table 1 pone.0350186.t001:** Eligibility criteria for participation in the STEP-TB cohort.

Category	Criteria
Inclusion criteria	1. Aged ≥ 19 years.
	2. Individuals eligible for LTBI testing or treatment who meet one or more of the following conditions: • Contact of a patient with infectious TB. • Person living with HIV. • Receiving or scheduled to receive immunosuppressive therapy. • Planned treatment with TNF antagonists, other biologic agents, or small-molecule inhibitors. • Presence of fibrotic or calcified lesions suggestive of spontaneously healed TB on chest radiograph. • Receiving or scheduled to receive prolonged corticosteroid therapy. • Having autoimmune disease. • Having chronic kidney disease, including those on dialysis. • Having hematologic malignancy or solid tumor. • Having diabetes mellitus. • History of or planned gastrectomy. • Having chronic lung disease (e.g., COPD, asthma, occupational or environmental lung disease). • Confirmed LTBI conversion within the past 2 years. • Healthcare worker. • Personnel working in congregate settings with a high risk of TB transmission (e.g., hospitals, schools) according to the TB Prevention Act. • Individuals considered at high risk for TB infection by local public health authorities (e.g., homeless persons, residents of shelters) under the TB Prevention Act.

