	3. Individuals scheduled for LTBI testing, those who have already completed testing with confirmed results, or those diagnosed with LTBI who have initiated, are receiving, or have completed LTBI treatment within 2 years.
	4. Capable of understanding study procedures, voluntarily consenting to participate, and providing written informed consent.
Exclusion criteria	1. Aged < 19 years.
	2. History of treatment for active TB disease.
	3. Any condition deemed inappropriate for participation by the principal investigator.

COPD, chronic obstructive pulmonary disease; HIV, human immunodeficiency virus; LTBI, latent tuberculosis infection; TB, tuberculosis; TNF, tumor necrosis factor

During the study period, when a patient meeting the eligibility criteria is identified, the attending physician will notify the study coordinator or investigator. The investigator will review the patient’s eligibility according to the inclusion and exclusion criteria, provide a thorough explanation of the study objectives, procedures, potential risks, and personal data protection, and obtain written informed consent from those who voluntarily agree to participate. Eligible participants who have provided consent will then be formally enrolled in the study.

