### Study population and analytic framework

After enrollment, all individuals referred for LTBI testing will constitute the source population of the cohort and will be described in terms of baseline characteristics (Table 2). Participants will then be followed according to their LTBI test results and subsequent treatment status (Fig 1). Individuals with negative LTBI test results will be followed to monitor progression to active TB. Among those with positive LTBI test results, participants will be categorized according to whether they receive TPT. Participants receiving TPT will be followed for both adverse events related to TPT and the development of active TB. Participants with positive test results who do not receive TPT will be followed to evaluate the incidence of active TB for comparative assessment.

**Table 2 pone.0350186.t002:** Study populations and outcomes in the cohort.

Study population	Description	Purpose of analysis	Outcomes assessed
All individuals referred for LTBI testing	High-risk population undergoing LTBI testing	Description of source population	Baseline characteristics
LTBI test negative	Participants with negative LTBI test results	Assessment of natural risk of TB among test-negative individuals	Incident active TB
LTBI test positive	Participants with positive LTBI test results	Population eligible for TPT	Stratified analyses according to TPT status
LTBI positive, TPT treated	Participants receiving tuberculosis preventive treatment	Primary safety analysis population	Adverse events related to TPT; Incident active TB
LTBI positive, TPT not treated	Participants with LTBI who do not receive TPT	Comparative assessment of TB risk	Incident active TB

LTBI, latent tuberculosis infection; TB, tuberculosis; TPT, tuberculosis preventive treatment

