### Outcome measures

The primary outcome is adverse events leading to permanent discontinuation of any drugs in the TPT regimen. This outcome will be defined as any clinical or laboratory event occurring during TPT that results in permanent discontinuation of one or more drugs in the prescribed regimen. For example, in patients receiving a 3HR regimen, discontinuation of rifampicin due to adverse events while continuing isoniazid to complete TPT will be considered as meeting the primary outcome.

The secondary outcomes are completion of TPT, the cascade of care for TPT, and the preventive effectiveness of TPT. TPT completion will be defined as completion of the prescribed TPT regimen within the recommended treatment period according to national guidelines. TPT cascade of care will be described by evaluating the proportions of individuals who are eligible for TPT, initiate treatment, and successfully complete treatment. The preventive effectiveness of TPT will be evaluated the incidence of progression to active TB during the follow-up period.

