CKD is an important high-risk condition that warrants inclusion in this study because it is consistently associated with a markedly increased risk of TB [12], largely driven by reactivation of latent infection rather than new exposure. As renal function declines, particularly in patients approaching or receiving dialysis, immune dysregulation substantially increases the likelihood of progression from LTBI to active TB disease, with reported TB incidence in dialysis populations far exceeding that of the general population [13]. In addition, TB in patients with CKD often presents atypically, leading to delayed diagnosis, poorer outcomes, and increased risk of transmission within dialysis units, thereby posing both individual and public health concerns [14]. Despite these risks, LTBI screening and treatment practices in CKD remain highly variable, largely due to diagnostic uncertainty and concerns about treatment-related adverse events, and robust, condition-specific safety data are lacking [15,16]. Recent reviews [17] have highlighted the urgent need for prospective evidence to better define the balance of benefit and harm of LTBI treatment in CKD populations and to support more consistent, evidence-based preventive strategies. By including patients with CKD across disease stages, the STEP-TB cohort is well positioned to address these critical evidence gaps and inform safer, more effective LTBI management in this high-risk group.

Importantly, this study is also designed to examine the cascade of care for LTBI [18,19], from diagnostic testing and treatment initiation to treatment completion, across different comorbidity groups. By systematically evaluating barriers and drop-offs at each step of the LTBI care continuum, STEP-TB will identify condition-specific hurdles faced by patients with complex medical comorbidities. Understanding these real-world challenges is essential for informing feasible and safe expansion of LTBI treatment policies, and the evidence generated by this cohort will directly support efforts to broaden preventive treatment strategies while maintaining patient safety.

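### The care cascade pools people who enter after a positive result or during or after TPT with people enrolled before testing, which biases observed initiation upward and probably completion too

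*Protocol article*

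**What the plan says.** Outcome measures defines the secondary outcome: "TPT cascade of care will be described by evaluating the proportions of individuals who are eligible for TPT, initiate treatment, and successfully complete treatment". Statistical analysis adds only that it will be descriptive. The Discussion gives the intended span, "from diagnostic testing and treatment initiation to treatment completion, across different comorbidity groups", and says the purpose is to find barriers and losses at each stage.

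Study population lists four routes into the cohort. The first is being scheduled for LTBI testing. The other three read: "2) have already completed LTBI testing, (3) are currently receiving TB preventive treatment, or (4) have completed TPT within the past two years". Inclusion criterion 3 in Table 1 repeats this and covers "those diagnosed with LTBI who have initiated, are receiving, or have completed LTBI treatment within 2 years". Recruitment works by notification: "when a patient meeting the eligibility criteria is identified, the attending physician will notify the study coordinator or investigator". Consecutive enrolment is not stated.

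Study population and analytic framework then describes a single starting population: "After enrollment, all individuals referred for LTBI testing will constitute the source population of the cohort". Nothing in the article separates participants by entry route or limits the cascade denominator to those enrolled before testing.

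**The concern.** A cascade proportion is informative when everyone in its denominator was observed from before the step in question, so that people who fail the step are counted alongside those who pass it. Three of the four entry routes begin after at least one step. Someone enrolled on TPT could not have been recorded as a non-initiator, and someone enrolled after finishing TPT could not have been recorded as a non-completer. Pooling them with pre-test entrants mixes two quantities: how care performs, and when patients came to the study's notice.

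The cascade is descriptive and secondary, and this point leaves the primary outcome untouched. But the article presents the cascade as evidence for widening preventive treatment, overall and by comorbidity group. Initiation or completion proportions that are too high would understate the losses the study sets out to describe.

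**Working it through.** **The plan's own figure.** The only stated number that uses a cascade proportion is total enrolment: 548 / 0.40 = 1,370, which reproduces exactly. The Sample size calculation uses 40% both for being positive and starting TPT and for positivity alone, so it supplies no separate initiation proportion. The entry mix is not given anywhere. The inputs below are therefore assumptions, shown over a range.

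**What each entry route contributes by construction**

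| Entry route | Positive | Initiated | Completed |
|---|---|---|---|
| Scheduled for testing | observed | observed | observed |
| Result known, not on TPT | fixed at entry, either way | observed | observed |
| On TPT | yes | yes | observed, but early stopping already escaped |
| Completed TPT within two years | yes | yes | yes |

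**Initiation among positives.** Let *s* be the share of LTBI-positive participants who enter on or after TPT, and *i* = 0.60 the assumed true initiation. Observed initiation = *s* + (1 − *s*) × *i*.

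- *s* = 0.10: 0.10 + 0.90 × 0.60 = 0.64
- *s* = 0.40: 0.40 + 0.60 × 0.60 = 0.76

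**Positive to completed.** Assume 75% completion among initiators. The true value is 0.60 × 0.75 = 0.45.

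- If late entrants also complete at 75%: 0.64 × 0.75 = 0.48 and 0.76 × 0.75 = 0.57.
- If every late entrant completes: 0.10 + 0.90 × 0.45 = 0.505 and 0.40 + 0.60 × 0.45 = 0.67.

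The second line is a ceiling. Completion is certain only for those who enter having already finished TPT; those on TPT can still stop.

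**Completion among initiators.** If 20% of initiators enter with TPT already completed and true completion is 70%, observed completion is 0.20 + 0.80 × 0.70 = 0.76.

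**Cross-check on all enrollees.** Let *f* be the share of all enrollees who enter on or after TPT, with the rest entering before testing. Take positivity of 40% from the protocol and assume initiation of 70%. At *f* = 0.20:

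- observed positivity = 0.20 + 0.80 × 0.40 = 0.52
- observed initiation among positives = (0.20 + 0.80 × 0.40 × 0.70) / 0.52 = 0.424 / 0.52 = 0.815

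At *f* = 0 the formulas return 40% and 70%, so the distortion comes entirely from the late entrants.

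**The case against.** The strongest reply is that the article fixes no cascade denominator. It names three proportions and calls the analysis descriptive, and denominators for such a table are often left to an analysis plan, which is not shown here. The framework speaks of people referred for testing and the sample size counts testing candidates, so most participants may enter before the test. This stands in part: the analysis plan may already restrict the denominator, and the bias could be small. But the entry routes and the single pooled source population are fixed in this article, and applying the outcome definition to that population gives the mixture shown above.

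A reader might go further and infer four things that the documents do not support.

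- *That people lost at a step cannot enter, so the cascade hides its drop-offs.* Pre-test entrants are followed through later losses. The already-tested route is open whatever the result or treatment. Table 2 has an untreated positive group, which Table 4 follows. Table 1 lists having initiated treatment separately from receiving or completing it, so early stoppers are not shut out. Under-representation is the most that can be said.
- *That result-known entrants inflate positivity.* That route admits negatives too; the direction depends on who is notified.
- *That comorbidity differences will be artefacts of each clinic's referral timing.* The article says nothing about referral timing by clinic. This is a possibility only.
- *That positive-to-completed would be 51–67%.* That range requires every late entrant to complete.

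**Conclusion.** The concern holds in a limited form. Participants who enter on or after TPT pass the positive and initiation steps by construction, and past completers pass the completion step as well. Pooled with pre-test entrants, they bias observed initiation upward. Completion is probably biased upward too, because on-TPT entrants have already avoided early discontinuation and early stoppers are less likely to come to notice.

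The size depends on an entry mix that the documents do not give. Under the assumed 60% initiation and a late-entry share of 10–40% of positives, initiation is overstated by 4 to 16 percentage points. With the assumed 75% completion applied to everyone, positive-to-completed is overstated by 3 to 12 points. The larger overstatement of about 6 to 22 points is an upper illustration. If few participants enter late, the effect is small. Participants enrolled before their result was known remain a valid base for the cascade, so the outcome can be rescued without changing enrolment.

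**What to change.** 1. Classify each participant's entry step (before result, result known and not on TPT, on TPT, TPT completed). The consent, test and TPT-start dates should allow this; otherwise add one case-report-form field.
2. Compute the cascade proportions, overall and by comorbidity, only in participants who consented before their LTBI result was known.
3. Result-known entrants not yet on TPT may be shown separately for initiation and later steps.
4. Leave on-TPT and post-TPT entrants out of the initiation and completion proportions, or show them separately and labelled as selected. Adding on-TPT entrants to the completion proportion would keep the bias towards people who have not yet stopped.
5. Report the number entering at each step, and state selection through physician notification as a limitation, because the restricted denominator does not remove it.

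The cost is at most one form field and a smaller cascade table, with less precision in the comorbidity subgroups. Eligibility, enrolment and care do not change.

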### Adverse event assessment

Adverse events are defined as any undesirable and unintended signs, symptoms, or diseases temporally associated with the use of a medicinal product, regardless of causal relationship, including abnormal laboratory findings. The definition and severity grading of adverse events will follow the Common Terminology Criteria for Adverse Events (CTCAE), version 5.0.[6] At the time points specified in Table 2, clinical symptoms, blood laboratory tests, and chest radiography will be assessed. Adverse events will be recorded using the standardized adverse event reporting forms provided in the S1 Table. The reporting form captures the presence of adverse events, the reported event term coded using the MedDRA terminology, data of onset and resolution, seriousness, severity grade according to CTCAE, causality assessment with anti-TB drugs, action taken, and clinical outcome of the event. Adverse events will be evaluated in terms of their type, frequency, and severity. The clinical significance of each event will be determined by the investigator based on medical judgment and patient condition.

### Treatment adherence and completion

Treatment adherence will be assessed based on patient self-report during scheduled study visits by comparing the total number of prescribed treatment days with the number of days the medication was actually taken. If treatment is discontinued, the reason for discontinuation will be recorded. Treatment completion will be determined according to the type and duration of the TPT regimen. Completion of the 9H will be defined as taking at least 80% of the prescribed doses within 12 months. For the 4R, completion will be defined as taking at least 80% of the prescribed doses within 6 months. For the 3HR, completion will be defined as taking at least 80% of the prescribed doses within 4 months.

### Ascertainment of incident active TB during follow-up

The occurrence of active TB during the follow-up period will be assessed through scheduled study visits and telephone follow-up when participants are unable to attend in person. At follow-up visits, participants will undergo clinical evaluation including symptom screening and chest radiography. If active TB is suspected based on symptoms or radiographic findings, additional microbiological testing, including sputum smear microscopy, nucleic acid amplification testing, and mycobacterial culture, will be performed according to standard clinical practice. Incident active TB will be defined as microbiologically confirmed or clinically diagnosed TB occurring after study enrollment during the follow-up period.

### Statistical analysis

Baseline characteristics of participants undergoing LTBI testing will be summarized using means and standard deviations for normally distributed continuous variables, medians and interquartile ranges for non-normally distributed variables, and frequencies with percentages for categorical variables.

To investigate if the presence of CKD alters the risk of adverse events (present/absent) during TPT, logistic regression models will be built, initially categorizing CKD as a binary variable (present/absent) and then as a ternary variable (present severe, present and not severe, absent). The minimal sufficient adjustment set for inclusion in adjusted models will be derived from a directed acyclic graph (DAG). Potential effect modification by CKD treatment will be explored amongst individuals with CKD. All statistical analyses will be performed using R or SPSS software. Additional analyses will be considered further categorizing the outcome, e.g., on the basis of adverse event severity (ordinal logistic regression) or taking into account the association between an adverse event and the drugs in use. P-values will be corrected for multiple testing.

Assessment of the association between CKD and TPT completion will take place similarly, as will progression to active TB, albeit here using time-to-event models. Finally, the cascade of care analysis will be descriptive.

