Building a prospective cohort to collect clinical information on LTBI‑positive individuals is needed to establish a research platform for answering these questions. In this manuscript, we provide an overview of the design, methods and scope of this cohort study. This Safety of Preventive Treatment in People at Risk for Tuberculosis (STEP-TB) study is supported by the Korea National Institute of Health as a national research project. The study findings and datasets will be used as scientific evidence for developing the national TB control master plan in accordance with the TB Prevention Act. We aim to provide evidence to inform national TB policy by evaluating the safety of TPT in the high‑risk groups for active TB disease.

Among the medical high-risk groups for TB, including individuals with chronic kidney disease (CKD), chronic lung disease, diabetes mellitus, malignancy, immunosuppressive conditions, and occupational exposure, the safety of TB preventive treatment remains an important clinical concern. CKD is of special interest because patients with CKD have an increased risk of TB and may be more vulnerable to drug-related adverse events. This study aims to evaluate the safety of TPT in individuals at high risk of developing active TB disease in Korea using a multicenter prospective cohort design. The primary objective is to specifically investigate whether CKD is associated with an increased risk of adverse events during TPT. The secondary objective is to assess the association between CKD and TPT completion, to describe the TPT cascade of care among individuals at high risk of TB, and to evaluate the preventive effectiveness of TPT in reducing progression to active TB during the follow-up period. These objectives will allow a comprehensive understanding of both the safety and effectiveness of TPT in high-risk populations.

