VAMS sampling			O	O		
Questionnaire		O				

V, visit; D, day; W, Week; M, Month; EOT, End of Treatment; EOS, End of Study; TB, tuberculosis; VAMS, volumetric absorptive microsampling.

To assess the development of incident active TB, an additional follow-up visit will be conducted 12 months after TPT initiation (end of study).

To evaluate drug pharmacokinetics and pharmacogenetic profiles, blood samples will be collected using Volumetric Absorptive Microsampling (VAMS). VAMS collection will be performed at the planned visits (Week 2 and Week 4), precisely 3 hours (±5 minutes) after the participant takes the anti-TB medication. Participants will be instructed to take the medication at a consistent time in the morning before breakfast, and the exact time and date of drug administration and sampling will be recorded in the case report form.

For participants with negative LTBI results, or for those who test positive but do not receive TPT, follow-up assessments will be conducted at 6 months and 12 months after baseline, after which the study will conclude (Table 4). The occurrence of active TB will be evaluated throughout the follow-up period.

**Table 4 pone.0350186.t004:** Study visit schedule and assessments for participants with negative latent tuberculosis infection results or without tuberculosis preventive treatment.

Visit	V0	V1	V3	V4
Visit name	Screening	Baseline	6 months	EOS
Timing	−D14	D0	M3–10	M11–15
Informed consent	O			
Medical history	O	O	O	O
Chest imaging		O	O	O
Questionnaire		O		

V, visit; D, day; W, Week; M, Month; EOT, End of Treatment; EOS, End of Study

Study participation may be discontinued under specific circumstances. Participants who withdraw their informed consent will discontinue further study procedures. Investigator may also discontinue participant’s involvement if, in their clinical judgment, continued participation is deemed inappropriate due to medical, safety, or other relevant considerations. Participants who discontinue study participation will not be excluded from the analysis. Instead, all available data up to the point of discontinuation will be retained and reported where applicable.

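### The promised treated-versus-untreated comparison of TB progression names no TPT contrast in the analysis, and its follow-up clocks do not fit the enrolment of current and past TPT users

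*Protocol article*

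**What the plan says.** All references are to the protocol article.

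- **Objective.** The Introduction lists as a secondary aim "to evaluate the preventive effectiveness of TPT in reducing progression to active TB during the follow-up period". Outcome measures repeats it: "The preventive effectiveness of TPT will be evaluated the incidence of progression to active TB during the follow-up period".
- **Comparator.** Study population and analytic framework states: "Participants with positive test results who do not receive TPT will be followed to evaluate the incidence of active TB for comparative assessment". Table 2 adds that LTBI-positive participants will be analysed in strata of TPT status.
- **Analysis.** After describing logistic models for CKD and adverse events, Statistical analysis says: "Assessment of the association between CKD and TPT completion will take place similarly, as will progression to active TB, albeit here using time-to-event models". Nothing else there concerns TB progression.
- **Follow-up clocks.** Under Study procedures, for treated participants "an additional follow-up visit will be conducted 12 months after TPT initiation (end of study"; for test-negative or untreated participants "follow-up assessments will be conducted at 6 months and 12 months after baseline".
- **Event definition.** "Incident active TB will be defined as microbiologically confirmed or clinically diagnosed TB occurring after study enrollment during the follow-up period".
- **Eligibility.** Study population and Table 1 admit people currently on TPT and people who completed it within the past two years. The only TB-related exclusion in Table 1 is "History of treatment for active TB disease".

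**The concern.** The objective asks what TPT does to TB progression. The one analysis sentence on that outcome continues a series of CKD models, so a reader cannot tell that TPT is to be the exposure, or against whom and from what date.

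The dates matter because they differ by group. A treated participant's year starts when TPT starts, which may be long before enrolment. An untreated participant's year starts at study baseline. TB can be counted in either group only after enrolment. A prior TPT user therefore brings a stretch of treated time in which no event could have been recorded, and untreated participants have no matching stretch. If that time enters the denominator, TPT looks better than it is.

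A smaller worry points the same way. TB found at the baseline work-up, after consent, is not barred from counting as incident. Such a person would be unlikely to start TPT and could be counted among the untreated.

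The Introduction says the findings will serve as evidence for the national TB control master plan, so a bias towards TPT would matter.

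**Working it through.** The plan derives no event number, sample size or power for this objective; Sample size calculation covers only CKD and adverse events. There is no figure to reproduce, so the check sets the rules side by side and follows their arithmetic.

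**1. Three anchors**

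| Rule | Treated | Untreated |
|---|---|---|
| 12-month follow-up runs from | TPT initiation | baseline |
| TB counts from | enrolment | enrolment |
| Follow-up clock can start well before enrolment | yes (current and past users) | no |

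**2. Which time can hold an event**

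Suppose a prior user had developed TB between starting TPT and enrolling. If treated for it, that person is excluded by Table 1. If not, the diagnosis still predates enrolment and does not meet the event definition. Either way the interval is free of counted events by design.

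**3. When the window closes before enrolment**

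Take d as the nominal regimen length (section TB preventive treatment). The window from initiation has closed at enrolment if the time since completion exceeds 12 − d.

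| Regimen | d (months) | 12 − d (months) |
|---|---|---|
| 3HR | 3 | 9 |
| 4R | 4 | 8 |
| 9H | 9 | 3 |

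These limits are approximate, in both directions:
- Table 3 lets the final visit fall as late as month 15. Using 15 − d gives 12, 11 and 6 months.
- Treatment adherence and completion allows up to 4, 6 and 12 months to complete 3HR, 4R and 9H. Using those durations gives 12 − 4 = 8, 12 − 6 = 6 and 12 − 12 = 0 months.

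Eligibility runs to 24 months after completion, so the window can be closed under every variant. At the extreme, someone who finished 3HR 24 months ago started about 27 months ago, and month 12 passed 27 − 12 = 15 months before enrolment. For 9H it passed 33 − 12 = 21 months before.

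**4. Size if the time is credited**

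Assume no TPT effect, a constant TB rate, and 12 observed months after enrolment in both groups. Credit m event-free months to each prior user:

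apparent rate ratio = 12 / (12 + m)

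| m (months) | Ratio |
|---|---|
| 3 | 12/15 = 0.80 |
| 4 | 12/16 = 0.75 |
| 9 | 12/21 = 0.57 |
| 12 | 12/24 = 0.50 |

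This is the ratio for prior users only. If they are a fraction f of all treated participants, it becomes 12 / (12 + f·m). The documents give no f. With f assumed between 0.1 and 0.5 and m between 3 and 12, it runs from 12/12.3 = 0.98 to 12/18 = 0.67. If no time before enrolment is counted, this component returns to 1.0.

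**5. TB present at baseline**

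In Tables 3 and 4 consent is at V0 and baseline imaging at V1. The event definition has no lag and no exclusion for disease already present, so TB found at V1 fits its wording if enrolment is taken to follow consent.

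**The case against.** The strongest reply is that this is a condensed article and model detail belongs in an analysis plan that is not shown. That is fair for the model itself. Table 2 does announce a contrast by TPT status, so it would be wrong to infer that no such comparison is planned. Nor is a CKD adjustment set imposed on it: Statistical analysis gives a method for choosing confounders from a DAG, which would yield a different set for a different exposure. What remains is a sentence that points to CKD when the objective concerns TPT.

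A reader might also infer that every treated-versus-untreated comparison is biased. The documents do not support that. The clocks are visit schedules, and no model origin is stated. For new initiators, D0 in Table 3 is the start of treatment, so their own clock holds no immortal time. Nothing forbids restricting to them or starting the clock at enrolment. The bias arises only if time before enrolment is credited to treated participants.

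The reply is also largely right on baseline TB. Study procedures describes a work-up to exclude active TB, both visit tables schedule chest imaging at baseline, and the Introduction defines LTBI as asymptomatic with a normal radiograph. Baseline TB is thus an unguarded risk and not built into the design.

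What the reply does not answer is the conflict among rules that the article does fix: the treated clock, the event definition and the admission of past users. Followed literally, they give some participants a follow-up period that ended before they joined.

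**Conclusion.** The concern holds in limited form. The analysis text names no TPT contrast for an objective that needs one. The stated anchors do not fit together for current and past TPT users. New initiators are not affected by the event-free time.

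If pre-enrolment time is credited, the error favours TPT: an apparent rate ratio of 0.80 to 0.50 among prior users for 3 to 12 credited months with no true effect, and nearer 1 across all treated participants. These figures assume a constant rate and 12 observed months in each group. The share of prior users is not documented, so the effect on the whole cohort cannot be fixed.

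The documents also do not support an estimate of how far one misassigned TB case would move the result. They give neither a TB risk nor the number of untreated LTBI-positive participants, and their figure of 548 refers to TPT initiators. That few events will occur is an assumption, made because follow-up is about one year and the study is not sized for TB.

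This should be fixed. It does not threaten the primary safety objective.

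**What to change.** Add a short paragraph to Statistical analysis stating that:

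- Preventive effectiveness is analysed among LTBI-positive participants, with TPT as a time-varying exposure.
- Time zero is the same in both groups, namely the later of the positive LTBI result and enrolment, and no person-time before enrolment is counted.
- The main comparison uses participants not yet treated at enrolment. Current and past TPT users are reported separately, because a common time zero alone does not remove the selection of people who had already stayed well on or after TPT.
- The DAG adjustment set is derived for the decision to give TPT.
- TB diagnosed from the baseline work-up or from baseline specimens is excluded from the TB risk set.
- Incidence rates are given with exact intervals, and the comparison is labelled descriptive.

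Study procedures should also say what follow-up applies to someone whose 12 months from initiation have passed before enrolment.

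The change is to text and needs the dates of the LTBI result, enrolment, TPT start and TB diagnosis. The article plans analysis for October to December 2028, so the paragraph can be settled before results are known. The price is fewer treated participants in the main comparison and a more modest effectiveness claim.
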